## Abstract

**Background:**

Body dissatisfaction is highly prevalent in Latin America, including Colombia. However, culturally adapted, evidence-based interventions are lacking, although effective programs exist in Western countries. This protocol describes a cluster randomized controlled trial (cRCT) of an intervention to improve media literacy and decrease body dissatisfaction and related outcomes among adolescents in urban and rural schools in Colombia.

**Methods:**

We will recruit 1250 adolescents in 7th–10th grade (aged 11–17 years) to participate in a two-arm, cluster-randomized, open-label, controlled superiority trial in Colombia. Participating schools will be recruited by the research team. Participants will be randomized at the school level (1:1). Randomization blocks stratified by socioeconomic status (high vs. low) and geographical area (rural vs. urban) will be used to assign schools to either: (a) a school-based, four-session group intervention delivered over 2–4 weeks by trained facilitators (*n* = 625) or (b) a waitlist control group that will receive the intervention only after follow-up (*n* = 625). Participants need to be aged 11–17 years old, attending a participating school and class in grades 7 to 10, have written parental consent, and give written assent to be eligible for participation in this study. Individuals who cannot understand spoken or written language, or who do not have parental consent to participate, will be excluded. Primary outcomes are media literacy and body dissatisfaction. Secondary outcomes include appearance comparison, thin ideal internalization, curvy ideal internalization (girls only), drive for muscularity (boys only), eating disorder symptoms, and general wellbeing. Additional exploratory outcomes include risky appearance-altering behaviours (girls only), colourism, and skin colour satisfaction. Furthermore, adverse outcomes will be recorded.

Outcome assessments will happen pre-intervention (baseline; Timepoint 1), 1-week post-intervention (immediate post-test; Timepoint 2), and 9–12 months post-intervention (follow-up; Timepoint 3).

**Discussion:**

Based on pilot data, we hypothesise that the intervention group will demonstrate increased media literacy and decreased body dissatisfaction at post-test and follow-up. We also anticipate improvements in secondary outcomes. This will be the first cluster RCT to evaluate the effect of a culturally adapted body image intervention in Colombia. This trial has been registered in the ISRCTN Registry (ISRCTN15802562, https://doi.org/10.1186/ISRCTN15802562). First enrolment was on 26th of August 2025.

**Trial registration:**

This trial has been registered in the ISRCTN Registry (ISRCTN15802562, https://doi.org/10.1186/ISRCTN15802562).

**Supplementary Information:**

The online version contains supplementary material available at 10.1186/s13063-026-09460-6.

## Introduction

### Background and rationale {6a}

Body dissatisfaction is a risk factor for eating disorders, depression, and low self-esteem [1–4]. School-based interventions to reduce body dissatisfaction and media literacy are a cost-effective way to foster resilience against appearance pressures and ultimately enhance mental health across diverse socio-economic contexts [5, 6]. However, only a few interventions have been tested in Latin American countries or rural areas so far [7]. In a cluster-randomized-controlled trial evaluating a comic-based body image intervention among Indian adolescents in semi-rural schools, participants in the intervention group reported higher body esteem (partial *η*^*2*^ = 0.01), lower eating pathology (partial *η*^*2*^ = 0.008), and reduced appearance-ideal internalization (partial *η*^*2*^ = 0.13) compared with controls. These effects were maintained at 3-month follow-up [8]. In rural Nicaragua, recent improvements in media access have increased risk for body dissatisfaction and eating disorders [9, 10]. A pilot study of a culturally adapted intervention program to promote body esteem and media literacy improved participants’ media literacy and reduced their internalization of the athletic ideal. Most participants also recalled key messages 6 weeks later, indicating good acceptability and feasibility of the program [11]. The current project will establish an evidence base and theoretical framework for body image education in Colombia, through the systematic evaluation of this intervention in Colombia. In a pilot study conducted in low socio-economic neighbourhoods of Barranquilla, Colombia, the intervention demonstrated high feasibility and acceptability among both students and facilitators. It produced substantial improvements in media literacy for both boys (partial *η*^*2*^ = 0.26) and girls (partial *η*^*2*^ = 0.27) at post-test, with these large effects sustained at 4-month follow-up. Additionally, girls showed moderate increases in body esteem (partial *η*^*2*^ = 0.06) and reductions in appearance-based social comparison (partial *η*^*2*^ = 0.07), which were maintained over the same period (manuscript in preparation).

### Objectives {7}

Evaluate whether participants randomized to receive the intervention show increased media literacy, decreased body dissatisfaction, and/or improvements in secondary outcomes at timepoint 2 and timepoint 3 compared to baseline, relative to participants randomized to the control group.

Assess effects of moderators (socioeconomic status (SES), school type, geographical location) on any observed changes in primary and secondary outcomes in response to the intervention.

### Trial design {8}

In this two-arm cluster-randomized, open-label, controlled superiority trial, we will compare changes in primary and secondary outcomes in participating adolescents randomized to receive either the intervention or a wait-list control condition in a parallel group design over the first 9–12 months of the study. The group allocation ratio is 1:1, clustered by school and stratified by geographical location (urban/rural), socioeconomic position (high/low), and funding status (state/private). Participants in the waitlist control group will receive the intervention after follow-up data collection is concluded.

## Methods: participants, interventions, and outcomes

### Study setting {9}

This project will run full assessments of the effectiveness of the program with adolescents attending 7th to 10th grade (typically 11–17-year-olds) in urban and rural Northern Colombia. Trained facilitators (paid research assistants) and students will deliver materials during the school day. Schools will be recruited through word of mouth and researcher contacts. All intervention activities are classroom-based and will be delivered to mixed-gender groups of 20–40 participants during class time. Outcome assessments will also be completed during the school day, in classrooms. Materials have been refined based on prior pilot study data with adolescents in the city of Barranquilla (*N* = 338). Quantitative assessments will use a wait-list control design, with outcomes measured at baseline, immediate post-test, and follow-up (9–12 months later). We are using translated and validated scales to assess body image, sociocultural internalization, eating attitudes, and general wellbeing. Additionally, we are in the process of validating scales measuring appearance comparison, curvy ideal internalization, appearance-altering behaviours, and colourism attitudes. All scales have undergone psychometric evaluation and linguistic adaptation to ensure cultural relevance for the Colombian context in a sample of Colombian adults (*N* = 505; *M*_age_ = 21.48, *SD* = 2.96, range 18–30). 

In Colombia, all areas are classified into six socioeconomic strata (*estratos*) based on residents’ income and living conditions. *Estrato* 1 includes the lowest-income households, whereas *Estrato* 6 comprises the highest. This stratification system is used to determine public service subsidies and utility fees: lower strata receive financial assistance for basic services such as electricity and water, while higher strata pay increased rates to support social equity [12].

### Eligibility criteria {10}

Participants must meet the following criteria to be eligible for the study:Aged 11–17 yearsAttending a participating school and classWritten parental consentWritten child assent before the start of the studyIn school grade 7 to 10 (11–17-year-olds)Urban cluster: school is in an urban area, as classified by [13]Rural cluster: school is in a rural area [13]High socioeconomic status: schools located in areas defined as stratum (*estrato*) 4, 5, or 6Low socioeconomic status: schools located in areas defined as stratum (*estrato*) 1, 2, or 3.

If the participants meet any of the following criteria, they will not be eligible for the study:Aged ≤ 11 or ≥ 17 yearsDo not have written parental consentParticipants with mental health conditions (e.g. active eating disorders) are not excluded from the study; however, parents are explicitly advised to think carefully about whether consenting to their child’s participation in the study is in their best interests in this situation and not to give consent if they have any concerns.

### Who will take informed consent? {26a}

Schools in Northern Colombia will be contacted by the research team and invited to participate in the study. Following approval from school principals, written study information will be distributed to parents. Parents will be required to provide written informed consent for their adolescent children to participate by returning a signed consent form to the team via the school or by completing a secure online form (hosted on Qualtrics). Adolescents (11–17-year-olds) will receive both written and verbal information about the study before filling out baseline questionnaires and will be asked to provide informed assent to participate. Only participants with valid parental consent and their own assent will be included in this study. Parental consent and adolescent assent will be collected by a member of the research team.

### Additional consent provisions for collection and use of participant data and biological specimens {26b}

Not applicable. This study is limited to self-report questionnaire data and does not involve the collection of biological specimens.

## Interventions

### Explanation for the choice of comparators {6b}

Trained facilitators (psychologists) will deliver the intervention, while participants in the control group will be assigned to a waitlist. All facilitators will undergo comprehensive training in intervention delivery. The waitlist control group will receive the same intervention from the same facilitators following the completion of follow-up assessments.

The waitlist control design was selected to allow for a comparison of intervention effects against “business as usual” for adolescents in Colombian schools, while ensuring ethical access to the program for all participants eventually. The use of a waitlist also facilitates the evaluation of long-term effects (via follow-up) before exposing the control group to the intervention. In the unlikely event that unanticipated and severe mental health outcomes emerge during implementation, we will re-evaluate the appropriateness of delivering the intervention to control groups, prioritizing the psychological well-being and ethical safeguarding of all participants. 

### Intervention description {11a}

The intervention, called “Soy Como Soy”, is a four-session, school-based intervention designed to promote positive body image (thus decreasing body dissatisfaction) and increase media literacy among adolescents in Colombia. Every session lasts 45 mins and is intended for mixed-gender classroom groups of children aged 11–17 years in their respective class age groups (20–40 participants).

The program targets the reduction of appearance-related pressures by teaching participants to critically analyse media messages, resist unrealistic appearance ideals, and support themselves and others in valuing non-appearance-related qualities. Each session incorporates psychoeducation, interactive discussions, and self-reflection exercises. The program is aligned with evidence-based change techniques for body image interventions [14] and has been pilot-tested in both Nicaragua [11] and Colombia (manuscript in preparation).

All sessions will be administered within a timeframe of 2 to 4 weeks, with either one or two sessions per week, depending on the school’s preference and availability. All sessions will be delivered during usual school hours and in a classroom setting. The facilitators will provide all materials necessary for the sessions (e.g. comic-based storyboards, paper, whiteboard markers).

### Criteria for discontinuing or modifying allocated interventions {11b}

At an early stage, intervention participation of a school can be discontinued if the school principal or staff are unresponsive or uncooperative. If only a small number of parents gave written informed consent in any given class (i.e., less than 30%) and enough consent forms cannot be obtained after a reminder, the research team can decide to switch to a different class. Recruitment will continue until the planned sample size is achieved.

Participants can leave the classroom during data collection and intervention sessions at any time without giving a reason. Participants’ participation can also be ended by facilitators if the participant is uncooperative and disruptive to the delivery of the sessions. Data that have been collected up to that moment will be included in the analysis.

A severe adverse event would be defined as an instance of significant and prolonged mental health crisis in an intervention group participant directly linked to their participation in the intervention. Facilitators will be trained to closely observe participants for signs of any distress and to immediately offer support and remove the participant from the intervention session. Facilitators will be instructed to immediately report any event that may approach the threshold for a severe adverse event to the study principal investigator (PI), in writing and, where possible, by telephone in addition. The study will be terminated prematurely if multiple adverse events occur or if the research team determines that the high ethical standards of the intervention can no longer be maintained. In case of the premature ending of the study, all participants and their parents will be informed through letters or emails. All data up to that moment will be included in the analysis. No adverse events occurred during the pilot trial of the intervention.

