### Recruitment {15}

Strong partnerships with schools were built through ongoing engagement activities between Universidad del Norte and local schools, beginning in 2022, which helped foster sustained interest and collaboration. Local organizations, such as Univoluntario, are involved in the project and have good connections with schools. All schools are approached via email, followed up with personal visits to the schools to present the project and receive approval from the school director. Parental consent forms will be collected during and after parent information events before the start of data collection.

Intervention sessions will be conducted during school hours, to maximize participant engagement and availability. Participants will receive little gifts (e.g. keyrings, wristbands) and snacks; the schools will receive books to thank them for their time and effort.

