### Concealment mechanism {16b}

Allocation is not concealed and will be revealed to both participants and the research team after randomization.

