### Implementation {16c}

An allocation sequence will be generated by the PI; they will assign schools to the intervention and control groups without knowing the name and exact location of the school. The study group will then be revealed to the research team and participating schools.

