## Assignment of interventions: blinding

### Who will be blinded {17a}

Participants, researchers, and facilitators will not be blinded, as it is impossible for them not to realize who received the intervention and who did not. Parental consent will be obtained prior to randomization. However, schools must be informed of the intervention schedule in advance to facilitate planning, allocate time for the sessions, and arrange travel. Participants will complete the questionnaires without prior knowledge of the upcoming intervention to minimize potential bias; they will be informed afterward regarding the timing and nature of the next activity.

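### Stopping rules that act after open allocation fall mainly on the intervention arm, and the protocol does not keep stopped schools and pupils in follow-up

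*Protocol article*

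**What the plan says.** The rules stand in the protocol article under *Criteria for discontinuing or modifying allocated interventions* {11b}.

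- **Schools.** At an early stage, which is not defined, "intervention participation of a school can be discontinued if the school principal or staff are unresponsive or uncooperative".
- **Pupils.** Facilitators may end the participation of a pupil who disrupts the sessions. Data gathered to that point enter the analysis.
- **Classes.** If fewer than 30% of parents in a class consent, even after a reminder, "the research team can decide to switch to a different class. Recruitment will continue until the planned sample size is achieved".

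On who knows the arm and when:

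- *Concealment mechanism* {16b}: "Allocation is not concealed and will be revealed to both participants and the research team after randomization".
- *Implementation* {16c}, of the principal investigator: "they will assign schools to the intervention and control groups without knowing the name and exact location of the school".
- *Who will be blinded* {17a}: "Parental consent will be obtained prior to randomization". Schools nevertheless receive the schedule ahead of time for planning. For pupils: "Participants will complete the questionnaires without prior knowledge of the upcoming intervention to minimize potential bias".
- *Recruitment* {15}: "Parental consent forms will be collected during and after parent information events before the start of data collection".

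The waitlist arm receives the programme only after follow-up data are in (*Trial design* {8}), and until then has no protocol to follow ({11c}).

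**The concern.** The trial randomises schools, is open, and takes every outcome by self-report. Its protection against bias is that the schools and pupils compared at Timepoints 2 and 3 are those that were randomised. A rule that ends participation in one arm only, applied at the discretion of people who know the arm, weakens that protection if stopping the sessions also ends data collection.

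Schools or pupils who cooperate poorly with a body-image programme may well differ in outcome from the rest. If they leave the intervention arm while their counterparts in the waitlist arm stay, the arms are no longer comparable. The mixed model in {20a} cannot restore a school that contributes no outcome data after allocation.

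**Working it through.** **Step 1. Whom each rule can reach, and what happens to the data.**

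| Rule in {11b} | Arm it can reach before follow-up | What the protocol says of later data |
|---|---|---|
| End a school's intervention participation | Intervention, as waitlist schools have no sessions yet | Nothing |
| End a disruptive pupil's participation | Intervention, for the same reason | Data so far are analysed; Timepoints 2 and 3 not mentioned |
| Switch a low-consent class | Either; blind to arm if consent precedes randomisation | Not applicable |
| Recruit on to the target | Either | {16a} randomises schools in blocks; {11b} does not refer to it |

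The first two rules can act after allocation is known, and they fall on one side. The sentence that keeps data so far follows the text on individual pupils and does not clearly cover a stopped school.

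The third rule depends on order. {17a} puts consent before randomisation, {15} ties it only to the start of data collection, and {11b} gives no timing under a heading about allocated interventions. The three are compatible, but only {17a} states the order that protects the trial.

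**Step 2. Size.** The protocol gives no expected number of stopped schools or pupils, so this is an illustration.

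Inputs from *Sample size* {14} and the abstract: d = 0.25, group size m = 25, ICC = 0.046, 251 per arm before clustering, 10% attrition, 625 per arm.

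- Design effect: 1 + (25 − 1) × 0.046 = 2.104. Check: 251 × 2.104 = 528.1, against the stated 529.
- Groups per arm: 625 / 25 = 25, so one group is 4% of an arm. These are classroom-sized groups. The number of schools is not given; a school with two or three classes would be 8% or 12%.
- Analysed per arm: 625 × 0.9 = 562.5. Standard error of the difference: √(2 × 2.104 / 562.5) = 0.0865 SD.
- If a share f of one arm is lost, and the lost differ from those retained by g SD, the retained mean departs from the full-arm mean by f × g.
- Two-sided type I error with bias b: 1 − Φ(1.96 − b/0.0865) + Φ(−1.96 − b/0.0865).

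| f (assumed) | g (assumed) | Bias, SD | Share of d = 0.25 | Type I error |
|---|---|---|---|---|
| 4% | 0.2 | 0.008 | 3.2% | 5.1% |
| 8% | 0.3 | 0.024 | 9.6% | 5.9% |
| 12% | 0.3 | 0.036 | 14.4% | 7.0% |
| 20% | 0.5 | 0.100 | 40% | 21% |

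**Step 3. How plausible is g?** With ICC = 0.046 the between-cluster SD is √0.046 = 0.214. For whole schools or classes, g = 0.3 means that those lost average 0.3 / 0.214 = 1.4 between-cluster SDs from those kept; g = 0.5 means 2.3. The model in {20a} also includes the baseline outcome, so g is only the difference left after that adjustment. The last row is therefore an extreme bound for clusters.

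**The case against.** The strongest reply has four parts.

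**The class switch is a consent-stage event.** Parental consent comes before randomisation and the allocator does not know the school, so the switch is blind to arm. This stands if the order in {17a} is followed. A reader might infer that the team may swap classes knowing the arm; the protocol does not say so. It only fails to repeat the order where the switch is defined.

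**Nothing describes refilling an arm.** A reader might take continued recruitment to mean replacement within an arm. The text does not support that, and {16a} points to randomising new schools. This stands.

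**Pupils do not learn their arm before baseline.** A reader might see a conflict between {16b}, which reveals allocation after randomisation, and {17a}. There is none: {16b} does not place the disclosure before baseline, {17a} says pupils are told after the questionnaires, and {26a} has information and assent before the baseline questionnaires. This stands too.

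**A stopped school is not said to be deleted, and the analysis set may be in the SAP.** It is true that no deletion is stated. But whether Timepoints 2 and 3 are still collected is a matter of conduct. {11b} does address what happens to data when participation ends, and stops at the data in hand. The planned MNAR sensitivity analyses would help to show how much unobserved outcomes matter, but they replace data with assumptions where the pupils could simply be asked.

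**Conclusion.** The point holds for the stopping rules. Followed as written, {11b} permits loss to Timepoints 2 and 3 that depends on arm, in an unblinded trial with self-reported outcomes. For the class switch the point is narrower: the protecting order exists in {17a} but is not carried into {11b}.

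The size is unknown. It runs from negligible (0.008 SD, type I error 5.1%) to material (0.036 SD, about 14% of the planned effect, type I error 7.0%) under assumed losses of 4% to 12% and residual differences of 0.2 to 0.3 SD. Biases of a third or more of d = 0.25 can be computed, but they need many stopped schools that are also very unlike the rest, which sits poorly with the protocol's own ICC and ignores baseline adjustment. The documents do not support claiming them. The change is worth making because it is cheap and recruitment is expected to run to August 2027.

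**What to change.** Amend {11b} to state that:

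1. class selection, any class switch and parental consent are complete before the school is randomised, in line with {17a};
2. schools, classes or pupils whose intervention is stopped after randomisation remain in the analysis as randomised, and are still asked for Timepoints 2 and 3 unless consent or assent is withdrawn;
3. schools recruited later to reach the target are randomised under {16a}.

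Keep the rule in {17a} that pupils complete baseline before being told their arm, with assent taken beforehand as in {26a}. Schools can still receive their schedule in advance, so the planning needs named in {17a} are met. The grounds for stopping sessions are not touched.

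The cost is a few sentences and some extra follow-up effort in stopped schools, a few of which may still decline.

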*ideal internalization* will be assessed using the *Curvy Ideal Internalization scale* (CII). This questionnaire is answered on a 5-point Likert scale from *strongly disagree* (1) to *strongly agree* (5). Higher average scores indicate higher curvy ideal internalization (range 1–5). The original version was validated in the USA and contained 11 items [21]. The Latin American Spanish version was validated in Colombian women (*N* = 505, M_age_ = 21.48, SD = 2.96), contains 9 items, and achieved excellent reliability, ω = 0.92 ([name] et al., manuscript under review).*Boys’ drive for muscularity* will be assessed using the subscale *Muscularity-Oriented Body Image* (MBI) of the *Drive for Muscularity Scale* (DMS). This questionnaire is answered on a 6-point Likert scale from *never* (1) to *always* (6). Higher average scores indicate a higher drive for muscularity (range 1–6). The subscale contains 7 items [22]. The Spanish version was validated in adolescent boys from Spain and yielded excellent reliability (Cronbach’s *α* =.92) [23].*Eating disorder symptoms* will be assessed using the short version of the *Eating Disorder Examination Questionnaire* (*EDE-QS*), which assesses the frequency of eating disorder symptoms over the last week and contains 12 items [24]. This questionnaire is answered on a 7-point Likert scale from *0 days* (0) to *every day (6)* [7]. This version reached excellent reliability in British adults (Cronbach’s *α* =.91). We used the Spanish translation validated in adolescents from Spain [25].*General wellbeing* will be assessed using the *WHO-5 Wellbeing Questionnaire for Adolescents*, which contains 5 items [26, 27]. The questionnaire is answered on a 5-point Likert scale from *never* (1) to *all the time* (5). Higher average scores indicate higher general wellbeing (range 1–5). The Spanish version was validated in Colombian adolescents and yielded acceptable reliability, *ω* =.68 [28].

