### Interim analyses {21b}

An interim data analysis will be conducted once all immediate post-test data (Timepoint 2) have been collected. Final analyses will be performed after the completion of data collection at follow-up (Timepoint 3). This interim analysis will ensure data quality and participant safety before the follow-up phase. The intervention will be stopped if a significant increase in clinically concerning eating disorder symptoms or other adverse effects is detected.

Interim results will be shared internally with the research team, advisors, and relevant stakeholders, and may also be presented at academic conferences. These findings will not be published until the follow-up phase is complete; however, we may conduct and share secondary analyses of baseline variables prior to final publication.

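### The severe adverse event definition builds in both the arm and the cause, so mental health crises have no control-arm reference for the safety decisions

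*Protocol article*

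**What the plan says.** Section {11b} of the protocol article gives its only definition of a harm event: "A severe adverse event would be defined as an instance of significant and prolonged mental health crisis" occurring "in an intervention group participant directly linked to their participation in the intervention". On detection, the same section says "Facilitators will be trained to closely observe participants for signs of any distress", and tells them to report to the principal investigator anything that comes near the threshold. It then adds "The study will be terminated prematurely if multiple adverse events occur", without a number or a comparison between arms.

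Interim analyses {21b} places an analysis after Timepoint 2 ("An interim data analysis will be conducted once all immediate post-test data (Timepoint 2) have been collected") and attaches a rule: "The intervention will be stopped if a significant increase in clinically concerning eating disorder symptoms or other adverse effects is detected". It names no comparator and does not use the term severe adverse event.

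Explanation for the choice of comparators {6b} says that delivery to the control groups will be reconsidered if severe and unexpected mental health outcomes appear.

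Two other places mention harms without limiting them to an arm. The Methods paragraph of the abstract says "adverse outcomes will be recorded", and Adverse event reporting and harms {22} describes reporting to the principal investigator, the ethics committee and the advisory group. Neither defines the event.

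**The concern.** In a randomised trial the control arm shows how often an event happens without the programme. That requires the event to be defined so that it can occur in either arm, with the question of cause kept apart. Here the arm and the cause are both conditions for the event to exist.

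Two errors become possible, in opposite directions. A crisis that would have occurred anyway may be attributed to the programme, with no waitlist figure to set beside it. A crisis that the programme did provoke may be judged unlinked and disappear from the count. Who will be blinded {17a} states that participants, researchers and facilitators all know the allocation, and section {21a} states that there is no data monitoring committee. The safety conclusion on crises would then rest on unblinded attribution, although a randomised comparison is available. Analysis cannot repair this later, because events that were never recorded cannot be recovered.

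**Working it through.** The protocol states no figure on this point, so the check is mainly a comparison of passages.

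**1. What can be counted under the {11b} definition**

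| Event | Intervention arm | Waitlist arm |
|---|---|---|
| Crisis judged linked to the programme | counted | impossible by definition |
| Crisis judged unlinked | not counted | not counted |

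The waitlist count is 0 of 625 (planned arm size from the abstract), whatever its pupils experience.

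**2. Which decisions could use these events**

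- {11b}: ending the study if several adverse events occur.
- {21b}: stopping the intervention on an increase in adverse effects other than eating disorder symptoms.
- {6b}: reconsidering delivery to the control groups.

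None of the three repeats the defined term. Since {11b} holds the only event definition in the article, it is the natural one to apply, but that step is an inference.

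**3. Whether either reading of an increase in {21b} works for such events**

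- Against the control arm: the reference is zero by construction.
- Against baseline: no count can exist before the intervention for an event that must be linked to it.

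Neither reading gives a usable reference.

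**4. Whether the questionnaires fill the gap**

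Outcomes {12} has all scales completed at all three timepoints and compared between arms. This covers EDE-QS and WHO-5, so eating disorder symptoms, the one harm that {21b} names, have a proper control reference. But EDE-QS is a scale "which assesses the frequency of eating disorder symptoms over the last week and contains 12 items". Timepoint 2 is 1 week after the intervention and Timepoint 3 is 9–12 months after it, so an episode that starts and resolves between them falls outside the recall period. None of the listed scales records a crisis or a referral.

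**5. What a fixed zero does to a comparison (illustration only)**

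The protocol plans no such test. With k events among 625 intervention pupils and 0 among 625 waitlist pupils, the two-sided Fisher exact p-value is 2 × C(625, k) / C(1250, k):

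- k = 5: p = 0.062
- k = 6: p = 0.031

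Six linked events would therefore cross 0.05 even if the waitlist arm had had just as many crises. The calculation ignores clustering by school. It shows only that the zero is a product of the definition and carries no information.

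**The case against.** **The definition serves discontinuation.** It sits in the section on discontinuing the intervention, where a link to the intervention is a natural condition, while {22} and the abstract set no limit by arm. This stands in part: adverse events in general are undefined, not confined to one arm. But those places supply no definition that works in both arms, so the {11b} wording remains the only one.

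**A reader might infer that harms as a whole cannot be compared between arms.** The documents do not support that. EDE-QS and WHO-5 are collected and compared in both arms.

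**A reader might infer that {21b} contradicts {11b} by presupposing a comparison between arms.** That goes too far. {21b} names no comparator, could mean a change from baseline, and could intend its remaining adverse effects to be worsening on scales. The supportable point is that the text does not settle this and that, for crises, neither reading works.

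**A reader might infer that all unlinked or late harms are lost.** Facilitators must report near-threshold events, and the team keeps in touch with schools and offers referrals ({30}). A journal article may also leave adverse event forms to the full protocol, so silence on detection between Timepoints 2 and 3 is not itself a fault. The stated definition is.

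**A reader might want a count of background crises.** Multiplying an assumed rate over 9–12 months by 625 would not be valid. The detection route described runs through sessions delivered over 2–4 weeks, and only crises judged linked would enter the count. No background rate is given.

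**The remedy is not free.** Section {26b} limits the study to self-report questionnaire data, so a form on crises and referrals would widen it. That stands, and is included in the cost.

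**Conclusion.** The concern holds in a limited form. The {11b} definition gives a one-sided count: no waitlist crisis can qualify, and an intervention-arm crisis qualifies only if it is judged linked by people who know the allocation. Mental health crises therefore lack a control-arm reference for the decisions in {6b}, {11b} and {21b}, and {21b} leaves open what its increase is measured against.

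The scope is confined to severe adverse events as defined. The primary analyses and the EDE-QS and WHO-5 comparisons are unaffected. The direction of bias is unknown: unblinded attribution could raise the count or lower it. Its size cannot be estimated from the document.

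The conclusion assumes that no fuller document replaces the definition with one that applies to both arms, and that the defined event is the one meant in the three decisions.

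**What to change.** 1. Define the event (mental health crisis, clinical referral) without reference to arm or cause.
2. Record it in both arms on the same short form at Timepoints 2 and 3.
3. Record relatedness to the intervention as a separate field, and tabulate events by arm with and without it.
4. Reconcile {11b}, {21b} and {22} on which events are recorded, in which arms, and against which comparator an increase is judged. The stopping decision itself remains with the investigators.

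Cost: a protocol and ethics amendment, possibly with revised consent information, and a small amount of additional sensitive data on minors. Field cost is low, because research assistants are already present when questionnaires are completed ({18a}). They may not know of referrals, so the school contact may need to help complete the form. Recruitment began in August 2025 and is expected to run to August 2027 (Trial status), so schools enrolled later can be covered in full. Schools already past Timepoint 2 would be covered only from their next assessment.
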